### Study Design

This study utilizes a cross-sectional design with a short-term follow-up post meal for blood glucose monitoring, from July 30 to October 5, 2024, at the Ukrida Hospital, Jakarta, Indonesia. There was an a priori aim to assess the measurement error of the 4 groups, males and females with diabetes and without diabetes, separately. A sample size of 200 for each group was determined using the methods described by Bland and Altman [19]. Hence, a total sample size of 800 was required to provide a 95% CI of ±0.24×SD. Allowing for about 10% dropout, a total sample size of about 890 subjects was planned for recruitment.

The study will explore BGEM blood glucose prediction capabilities compared to laboratory blood analysis from capillary or plasma blood samples, with the study workflow summarized in Figure 1. The subjects were given an explanation on the study, asked for informed consent, and given a numeric identity tag to ensure anonymity of the dataset after undergoing a minimum of 8 hours of fasting before admittance to the study. Subjects undertook weight, height, waist circumference, and blood pressure measurement using GEA ZT120 body scales, tape measure roll, and Beurer BM26 sphygmomanometer, respectively. BMI scores were calculated from the weight and height of the subjects to evaluate obesity or metabolic condition of the subjects.

**Figure 1. F1:**
[figure not shown]
A conceptual framework of study design from recruitment, data collection, to discharge for 473 participants who self-acknowledged having diabetes mellitus (DM) and 412 participants who did not (non-DM).

Subsequently, each participant’s photoplethysmography data at the fasting time point (the first time point) were collected using both a smart ring (JC Smart Health Ring 2301B) and a smartwatch (Actxa Spark+Series 2), both provided by Actxa Pte Ltd. Simultaneously, blood samples were obtained from 2 sources: capillary blood for glucose concentration measurement using Accu-Chek (Roche) and plasma blood from the cubital vein for laboratory analysis, as described in a later section.

Participants then consumed a 552-kcal meal set with 79.8 g of carbohydrate content prepared by Ukrida Hospital. This meal was chosen to ensure adequate sustenance and satiety after overnight fasting, as sugary drinks alone may not sufficiently fulfill. The nutritional composition of the meal is detailed in Textbox 1 and Table S1 in Multimedia Appendix 1.

Textbox 1.Nutritional value of the set meal for the subjects, given after subjects fast for a minimum of 8 h and undergo first blood sample collection and photoplethysmography reading from wearables.Energy (kcal): 552.1Water (g): 241.8Protein (g): 19Protein percentage: 13.8Fat (g): 19.3Fat percentage: 31.5Carbohydrate (g): 79.8Carbohydrate percentage: 57.8Dietary fiber (g): 5.2Polyunsaturated fatty acid (g): 1.8Cholesterol (mg): 33Vitamin A (µg): 1396.8Carotene (mg): 0.4Vitamin E (eq.) (mg): 0.8Vitamin B1 (mg): 0Vitamin B2 (mg): 0.1Vitamin B6 (mg): 0.6Total folic acid (µg): 31.8Vitamin C (mg): 10.7Sodium (mg): 1015.5Potassium (mg): 549.4Calcium (mg): 59.2Magnesium (mg): 66.2Phosphorus (mg): 231.5Iron (mg): 2.5Zinc (mg): 1.6

Participants then underwent measurements at the second time point (1 h postprandial), third time point (2 h postprandial), and fourth time point (3 h postprandial). Photoplethysmography data collection followed the same procedure as the first time point using both the smartphone and the smart ring. For blood sample collection and testing, the third time point followed the same procedure as the first time point, with both capillary and plasma blood samples collected and analyzed. At the second and fourth time points, plasma blood collection was omitted, and only capillary blood samples were obtained and tested. Further details are provided in Table 1.

**Table 1. T1:** Blood glucose metabolism-related data collection from photoplethysmography sensors from 2 wearables, a glucometer, and blood samples based on several time points before and after meal.

Measurements	Smart ring^a^	Smartwatch^b^	Glucose meter^c^	Plasma blood^d^
First time point (fasting state)	Yes	Yes	Yes	Yes
Second time point (1 h postprandial)	Yes	Yes	Yes	No
Third time point (2 h postprandial)	Yes	Yes	Yes	Yes
Fourth time point (3 h postprandial)	Yes	Yes	Yes	No

a JC smart health ring 2301B.

b Actxa Spark + Series 2.

c Roche, ACCU-CHEK guide.

d Full blood count: Sysmex XN-550. Plasma glucose: Roche, Cobas c111 Analyzer. Hemoglobin A_1c_ level: Finecare FIA Meter III Plus.

During the 1-hour intervals at the last 3 time points, while waiting between data and sample collection, participants were asked to complete the International Physical Activity Questionnaire long form, along with questionnaires related to DM and other factors that may affect photoplethysmography reading and BGEM prediction that follows, such as skin type, treatment status, dominant hand, and race (Table 2).

**Table 2. T2:** Baseline study questionnaire and test descriptions collected from the study’s participants.

Questionnaire and test	Description of content	References
Demographic	Five items: age, gender, ethnicity, handedness, an Fitzpatrick skin type	[13]
Diabetic status and history	Six items: family history, status, year diagnosed, medication, gestational diabetes, and drink consumption	[13,20-23]
Relevant medical history	Four items: smoking, hypercholesterolemia, hypertension, and related medication	[13,21-23]
Physical activity	International Physical Activity Questionnaire (IPAQ) long form; 27 items	[24]
Clinical measurements	Four items: weight, height, waist circumference, and blood pressure	[13,20,21,23]
Pre-photoplethysmography measurements questions	Seven items: time of medication, time of meal, meal content, physical activity in 24 h, last, duration, and intensity	[12,25]

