## Introduction

Diabetes mellitus (DM) is a major noncommunicable disease that has affected around 500 million people worldwide and continues to rise up to 700 million people globally in 2045 [1]. Other noncommunicable diseases’ death risks have decreased by 20% since the turn of the century; DM, in contrast, has increased by 3% worldwide. The latest International Diabetes Federation Diabetes Atlas (2025) reports that 11.1% of the adult population (20‐79 y) is living with diabetes, with over 4 in 10 unaware of their condition.

Several reports have projected that about 1 in 2 adult patients with diabetes are unaware of their diagnosis [1-3]. Undiagnosed DM has resulted in an increase of cases with complications and elevated the burden of the disease, as younger undiagnosed DM cases have more rapid progression of complications and lower response to general DM treatment. This has been shown to be higher in low- and middle-income countries, where 80% of the DM population lived, thus reflecting the enormous burden of the disease [4,5]. Meanwhile, early diagnosis and treatment of DM reduce the risk and slow the progression of debilitating complications such as amputation, vision loss, renal failure, cardiovascular disease, dementia, some cancers, and infections including tuberculosis and severe COVID-19 [6]. All of the above calls for early screening and frequent monitoring strategies that are both effective and cost-efficient.

Currently available methods to detect DM are hemoglobin A_1c_ (HbA_1c_) level, fasting plasma glucose, 2-hour glucose tolerance test, and random plasma glucose test. All these methods are invasive; they require trained professionals and laboratory equipment to be performed correctly. The American Diabetes Association has recommended DM screening starting at 35 years and every 3 years after, especially for people with obesity, overweight, and one risk factor [7]. In low- and middle-income countries, this is even harder to implement due to the cost and scarce resources of such screening methods [5,6,8].

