Indonesia, a middle-income country with a population of 283 million, faces a big challenge in DM management. It was estimated that DM prevalence was 9.49% (2024) and will increase to 16.09% (2045) without any major effective intervention [9]. As in any other low- and middle-income countries, the cost and availability of DM-related testing have prohibited Indonesia from enacting an effective prevention or screening program; therefore, an affordable, effective, and simple screening or monitoring method for DM will be a boon in the national health program.

Photoplethysmography is a noninvasive optical technology that measures light absorbance to assess blood volume changes. It has been widely integrated into wearable devices, such as smartwatches, to monitor heart rate (HR) and other physiological parameters [10]. Emerging research suggests that photoplethysmography data may also be valuable for detecting DM and estimating glucose levels [11-13]. The noninvasive nature, affordability, and convenience of photoplethysmography make it a promising tool for early detection and preventive screening of DM, especially in large and diverse populations, such as in Indonesia. Despite photoplethysmography technology’s potential use in estimating blood glucose and DM prediction, several issues have been reported to influence its performance, such as medication status of subjects [14], motion artifacts [15], and also skin types [16]. This protocol paper will strive to address these issues to improve the reliability (accuracy and robustness) of photoplethysmography-based technology in wearable devices for blood glucose monitoring and DM risk prediction through advanced artificial intelligence (AI) and data analytics.

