## Methods

### Participant Recruitment

A total number of 885 participants from adults aged 18 years and above were recruited. These participants reside in the Greater Jakarta Area, Indonesia, and were from the diabetic exercise group, from staff and family members of Krida Wacana Christian University (Ukrida), and from its affiliated organizations. Participants were recruited using an online registration provided by the research team. Exclusion criteria were implemented as follows: BMI >37 kg/m^2^, diastolic blood pressure ≥120 mmHg, and systolic blood pressure ≥180 mmHg, wearing a pacemaker, having fever or any other acute critical illness during the data collection, and pregnant female participants. All subjects received an explanation on the study purpose, protocol, and risks, and also signed the informed consent prior to admission to the research study.

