### Blood Sample Analysis

All capillary blood samples were analyzed using the Accu-Chek Guide glucometer (Roche, USA). Cubital plasma blood samples were analyzed for full blood count using the Sysmex XN-550 (Sysmex, Japan), plasma blood glucose using the Cobas C111 Analyzer (Roche, Switzerland), and HbA_1c_ levels using the FineCare FIA Meter III Plus (Gongu Wondfo, China). These instruments were available at the Ukrida Hospital clinical laboratory. All hospital equipment was routinely calibrated according to the provider’s manual.

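### DM and non-DM status is self-reported, with no stated check against the laboratory results on file; the reference label for the discrimination metrics and the diabetes-risk target should be laboratory-supported

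*Protocol article*

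**What the plan says.** The only classification of diabetes status in the protocol article is the participant's own statement. The Figure 1 caption (Methods, Study Design) describes "473 participants who self-acknowledged having diabetes mellitus (DM) and 412 participants who did not (non-DM"). Table 2 shows that status was a questionnaire item: "Six items: family history, status, year diagnosed, medication, gestational diabetes, and drink consumption". The same 473 and 412 become participants with and without diabetes in Results, and the 473 become a Type 2 DM row in Table 3, although none of the questionnaire items listed asks for diabetes type.

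The Introduction states that "about 1 in 2 adult patients with diabetes are unaware of their diagnosis" and, from another source, that "11.1% of the adult population (20‐79 y) is living with diabetes, with over 4 in 10 unaware of their condition". It also lists HbA1c and fasting plasma glucose among the available ways to detect diabetes.

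Both were measured. Blood Sample Analysis gives "plasma blood glucose using the Cobas C111 Analyzer (Roche, Switzerland), and HbA_1c_ levels using the FineCare FIA Meter III Plus". Table 1 places a plasma sample at the fasting time point, and Non-Photoplethysmography Data Preprocessing reports no missing or invalid automated blood results. No section uses these results to set or check diabetes status; the Discussion mentions HbA1c only as a factor that may influence prediction.

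Status is used in several places. It defines the four sex-by-diabetes groups that sized the study (Study Design) and is one of seven non-photoplethysmography model features. Model Training names diabetes risk as a possible target. Statistical Analysis plans AUC, sensitivity, specificity and F1 without naming the reference label.

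**The concern.** A participant who does not report diabetes is not thereby free of it, and the article's case for the tool rests on that fact. If the self-reported grouping is the reference for the discrimination metrics, a model that correctly flags an undiagnosed participant is charged with a false positive. If it is the target for diabetes risk, such participants enter training as negatives. In both cases the people whom screening is meant to find are scored on the wrong side, although results that could identify many of them are already on file.

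**Working it through.** **The plan's own figures.** 473 + 412 = 885, and 473/885 = 53.4%. The sample size reproduces: the half-width of the 95% CI for a limit of agreement is 1.96 × √(3/200) = 0.240 SD; 4 × 200 = 800; 800/0.9 = 889, which matches the planned figure of about 890. The labelling question does not touch this calculation.

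**Inputs for the share of undiagnosed cases in the non-DM group.**
- Prevalence p: 9.49% (Indonesia, 2024) or 11.1% (adults aged 20-79 years), both from the Introduction and both read as total prevalence.
- Unaware share of cases u: 40% to 50% (Introduction).
- Non-DM group: 412 (Figure 1 caption).

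Among people without a known diagnosis, the share with diabetes is c = p·u / [1 − p·(1 − u)].

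| p | u | c | c × 412 |
|---|---|---|---|
| 9.49% | 40% | 0.03796/0.94306 = 4.0% | 16.6 |
| 9.49% | 50% | 0.04745/0.95255 = 5.0% | 20.5 |
| 11.1% | 40% | 0.0444/0.9334 = 4.8% | 19.6 |
| 11.1% | 50% | 0.0555/0.9445 = 5.9% | 24.2 |

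**Effect on apparent specificity if self-report is the reference.** Sensitivity (Se) and specificity (Sp) are not given for this study. I assume Se = 0.85 and Sp = 0.90.
- If undiagnosed cases are flagged as often as diagnosed ones, apparent Sp = (1 − c)·Sp + c·(1 − Se), a fall of c·(Se + Sp − 1) = 0.75c. At c = 4.03% this is 3.0 points (90% to 87.0%); at c = 5.88% it is 4.4 points (90% to 85.6%).
- If undiagnosed cases score midway between the groups, they are flagged with probability (0.85 + 0.10)/2 = 0.475. The fall is (0.475 − 0.10)·c = 0.375c, or 1.5 to 2.2 points.
- In the first case 0.85 × 16.6 = 14 to 0.85 × 24.2 = 21 correct detections would be counted as errors.

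**Effect on apparent AUC, with an assumed true AUC of 0.90.** If undiagnosed cases score like diagnosed ones, apparent AUC = (1 − c)·0.90 + c·0.5, a fall of 0.4c, or 0.016 to 0.024.

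**Where the label does not act as reference.** Feature Extraction sets the regression target as finger-prick glucose. The Parkes grids compare a reading with a reference glucose value. In the four-group measurement-error analysis the error is predicted against measured glucose, so mislabelling changes who is in each group but not the reference.

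**Effect in the other direction.** Diabetes status is a listed model feature. If self-reported status were also the outcome, the predictor would contain the outcome and discrimination would be inflated.

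**The case against.** The strongest reply is that the article never says self-report is the reference standard. The quoted line is a figure caption describing participant flow, and recruiting a sample balanced on diabetes status before any blood is drawn plausibly has to rely on known status. Statistical Analysis leaves the reference label open, and a fuller analysis plan may fix it on laboratory values, in which case the false-positive mechanism does not arise. This stands, and it makes the bias conditional. It does not remove the point: self-report is the only classification the article gives, and Results and Table 3 restate it without the qualifier.

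Several stronger readings are tempting and are not supported:
- *Specificity and AUC are biased downward.* The reference is unnamed, and status as a model feature could push performance upward.
- *The model learns to call undiagnosed people healthy.* This does not hold for the glucose model, which is trained on measured glucose. Only the diabetes-risk target could be affected, and its definition is not given.
- *About half of the non-DM group is undiagnosed.* The 40-50% is a share of cases, not of people without a diagnosis.
- *Contamination is 10-15%.* That would mean 41-62 of 412 and, on the same assumed accuracy, a fall in specificity of 7.5 to 11 points. The support is weak: age and BMI in Table 3 pool both groups, and those of the non-DM group are not given. Participants "were from the diabetic exercise group, from staff and family members of Krida Wacana Christian University (Ukrida), and from its affiliated organizations", so population figures may not fit, but by how much is unknown until the laboratory results are tabulated.

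**Conclusion.** The point holds in a limited, conditional form. Diabetes status is self-reported, the article itself says 40-50% of cases are unaware, and laboratory results that could check the label are not said to do so. About 17-24 of the 412 non-DM participants (4.0-5.9%) would be undiagnosed cases if that group resembled the general population without a known diagnosis. Their presence is an inference, not a reported finding.

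If this grouping is the reference, apparent specificity falls by about 3-4 points under the assumed accuracy, and by about half that if undiagnosed cases score between the groups. These sizes assume that everyone who reports diabetes has it. The net direction remains open because of the status feature. The glucose regression and error-grid results stand. This is worth settling before discrimination results are reported, but it does not undermine the study as a whole.

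**What to change.** 1. Name one reference label for AUC, sensitivity, specificity, F1 and the diabetes-risk target: a known diagnosis or diabetes medication, or HbA1c or fasting laboratory plasma glucose in the diabetic range of a named guideline, chosen before the results are examined. Non-DM is then neither. Keeping known diagnosis and medication in the definition retains treated participants whose laboratory values may be controlled.
2. Report laboratory-positive participants without a diagnosis as a separate row, since they are the screening target.
3. Keep the self-reported grouping as a sensitivity analysis.
4. Do not use diabetes status as a predictor in any model where it is the outcome.
5. Rename the Table 3 row for the current study 'self-reported DM', and carry the same qualifier into Results.

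The cost is recoding data already on file. No new measurement is needed. The counts 473 and 412, and those of the four sex-by-diabetes groups, will shift.

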### Ethical Considerations

All protocols were performed under hospital’s medical staff supervision at all times. Ethics approval for the study has been obtained from the Ukrida Faculty of Medicine & Health Sciences ethical committee on July 15, 2024 (1779/SLKE/IM/UKKW /FKIK/KEPK /VII/2024).

### Blood Sample Analysis

All capillary blood samples were analyzed using the Accu-Chek Guide glucometer (Roche, USA). Cubital plasma blood samples were analyzed for full blood count using the Sysmex XN-550 (Sysmex, Japan), plasma blood glucose using the Cobas C111 Analyzer (Roche, Switzerland), and HbA_1c_ levels using the FineCare FIA Meter III Plus (Gongu Wondfo, China). These instruments were available at the Ukrida Hospital clinical laboratory. All hospital equipment was routinely calibrated according to the provider’s manual.

### Photoplethysmography Data Collection

In this study, 2 wearable devices were utilized: the Actxa Spark+Series 2 smartwatch and the JC Smart Health Ring 2301B. Both devices are equipped with a green light photoplethysmography sensor that captures photoplethysmography signals at 50 Hz, ensuring adequate signal quality for HR analysis.

During data collection, the smartwatch was worn on the participant’s nondominant wrist, positioned at least 2 finger widths away from the wrist bone. The smart ring, selected based on appropriate sizing, was worn at the base of the index finger on the same hand. To ensure optimal signal acquisition, the ring’s photoplethysmography sensor was positioned facing the inner side of the finger. Each photoplethysmography recording session lasted for 5 minutes. Participants were instructed to remain seated, maintain a relaxed posture, and minimize movement, with their nondominant hand resting on a table to reduce motion artifacts.

Photoplethysmography data were collected by the wearable devices and transmitted via Bluetooth to a smartphone. The smartphone then relayed the data via the internet to Actxa’s company server for storage and further analysis.

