### Photoplethysmography Data Preprocessing

Each photoplethysmography recording was required to be at least 4 minutes in duration. No recordings from this clinical trial were excluded based on this criterion.

One participant was absent for the fourth measurement (3 h after the meal). For this participant, the available time point data were retained for individual data point analyses. However, in the time-series analysis (see the section photoplethysmography Data Feature Extraction), the data were excluded due to the incomplete sequence.

Raw photoplethysmography signals were obtained from the smartwatch (16-bit binary) and smart ring (23-bit binary) devices. Raw photoplethysmography data were preprocessed using a previously developed pipeline incorporating frequency noise filtering and outlier correction [12].

During the signal preprocessing stage, the raw digital signals were first converted to analog values using the following formula:

$V_{i}=5\;\times \frac{Signal}{2^{16}}$  (for smartwatch data)

$V_{i}=5\;\times \frac{Signal}{2^{23}}$  (for smart ring data)

A Chebyshev Type II bandpass filter (0.3‐5 Hz) was applied to remove low- and high-frequency noise, including motion artifacts. Outliers were identified, when necessary, using a *z* score threshold of 3 SD from the mean and replaced with reasonable estimates via nearest-neighbor interpolation prior to HR variability feature extraction.

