### Photoplethysmography Data Feature Extraction

To accurately identify key temporal positions of the photoplethysmography waveform, potential systolic peaks were first detected using sign changes in the first-order difference of the photoplethysmography signal, specifically identifying transitions from positive to negative values. The leading and trailing troughs of the pulse wave were then detected by inverting the photoplethysmography signal and applying the same first-order difference and sign change method.

HR was then calculated using the key temporal positions. The measured HR was required to exceed 48 beats per minute. No recordings from this clinical trial were excluded based on this criterion.

Using the identified key temporal positions, a feature extraction module was then applied to the photoplethysmography data fragments to compute a comprehensive set of features. The panel of features was established in our previously reported model, which included 248 features related to HR, HR variability, waveform morphology, energy metrics, complexity measures, and continuous wavelet transform [12].

Prior to model training, feature selection techniques were applied to eliminate redundant features. This process was conducted exclusively on the feature set derived from photoplethysmography data and involved 2 stages. First, a self-correlation matrix was calculated, and features with a Pearson correlation coefficient >0.7 were removed to reduce multicollinearity. Second, the correlation between each remaining feature and the regression target—blood glucose levels measured via finger prick tests under different mealtime conditions—was assessed. A subset of features with the strongest correlations to the target variable was retained, with the final number determined empirically to optimize model performance.

To account for the varying feature magnitudes, Min-Max scaling was applied. Since the regression target (blood glucose values) exhibited a nonnormal distribution, a Box-Cox transformation was used for normalization. Following model prediction, an inverse Box-Cox transformation was performed to restore the predicted blood glucose levels to their original scale.

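### As written, the peak-detection rule leaves beat times on a 20 ms grid, which inflates short-term HR-variability features when variability is low; refining the peak times is a cheap improvement.

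*Protocol article*

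**What the plan says.** All of this is in the Methods of the protocol article.

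- **Photoplethysmography Data Collection.** Each device has a green-light sensor that "captures photoplethysmography signals at 50 Hz, ensuring adequate signal quality for HR analysis". Adequacy is asserted for heart rate only; nothing is said about HR variability. A recording lasts 5 minutes.
- **Photoplethysmography Data Preprocessing.** The article refers to an earlier report for the pipeline: "Raw photoplethysmography data were preprocessed using a previously developed pipeline incorporating frequency noise filtering and outlier correction". It then gives the main steps. "A Chebyshev Type II bandpass filter (0.3‐5 Hz) was applied to remove low- and high-frequency noise". Outliers are "replaced with reasonable estimates via nearest-neighbor interpolation prior to HR variability feature extraction". That is the only interpolation mentioned, and it replaces outliers rather than refining timing.
- **Photoplethysmography Data Feature Extraction.** For beats, "potential systolic peaks were first detected using sign changes in the first-order difference of the photoplethysmography signal". Troughs are "detected by inverting the photoplethysmography signal and applying the same first-order difference and sign change method". The positions are then carried forward: "Using the identified key temporal positions, a feature extraction module was then applied to the photoplethysmography data fragments". The panel, again taken from the earlier report, "included 248 features related to HR, HR variability, waveform morphology, energy metrics, complexity measures, and continuous wavelet transform". Features are later screened by their correlation with finger-prick glucose.

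**The concern.** A sign change of the first difference identifies a sample, not a time between samples. At 50 Hz the samples are 20 ms apart, so every beat time is rounded to the nearest 20 ms unless a further step refines it. Mean heart rate over 5 minutes hardly notices this. Short-term HR-variability measures can, because they are built from beat-to-beat changes that may be of the same order as the rounding step.

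The rounding variance adds to the true variance, so low values are lifted most and the contrast between people with low and high variability shrinks. These features are candidate inputs to the glucose and diabetes-risk models and must survive a screen on correlation with the target. Avoidable measurement error therefore enters at the point where features are chosen.

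**Working it through.** The article gives no figure for beat-timing or HR-variability error, so there is no stated result to reproduce.

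**Inputs from the article:** 50 Hz sampling; 0.3-5 Hz Chebyshev Type II filter; first-difference sign-change rule; 5-minute recordings.

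**Assumed, because the article does not give them:** true RMSSD from 5 to 60 ms; mean interval about 800 ms; rounding errors independent and uniform. The article does not name its individual HR-variability features. RMSSD and SDNN (the standard deviation of the intervals) are used here as standard examples.

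**Step 1: rounding error.** Step q = 1000/50 = 20 ms.
- One beat time: variance q²/12 = 400/12 = 33.3 ms², SD 5.8 ms.
- One interval (difference of two beat times): 2 × 33.3 = 66.7 ms², SD 8.2 ms.
- One successive difference of intervals (weights 1, -2, 1 on three beat times): (1 + 4 + 1) × 33.3 = 200 ms², SD 14.1 ms.

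**Step 2: mean heart rate.** The rounding errors cancel except at the first and last beat. The error in total duration has SD 8.2 ms in 300,000 ms, or about 0.003%, which is negligible.

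**Step 3: RMSSD.** Observed ≈ sqrt(true² + 200). The last column simulates 5-minute beat series with beat times rounded to 20 ms.

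| True RMSSD (ms) | Formula (ms) | Inflation | Simulated (ms) |
|---|---|---|---|
| 5 | 15.0 | +200% | 16.1 |
| 10 | 17.3 | +73% | 17.2 |
| 15 | 20.6 | +37% | 20.5 |
| 20 | 24.5 | +22% | 24.5 |
| 30 | 33.2 | +11% | 33.2 |
| 40 | 42.4 | +6% | 42.4 |
| 60 | 61.6 | +3% | 61.7 |

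Formula and simulation agree closely from 10 ms upward. Inflation drops below 10% once 0.21 × true² exceeds 200, that is, above about 31 ms. A true fourfold contrast (10 against 40 ms) becomes 42.4/17.3, about 2.4-fold.

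**Step 4: SDNN.** Observed ≈ sqrt(true² + 66.7). True 10, 20 and 50 ms read as 12.9, 21.6 and 50.7 ms, so SDNN is affected much less.

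**Step 5: does refinement work at 50 Hz?** Noise-free synthetic pulse waves were sampled at 50 Hz and passed through a Chebyshev II 0.3-5 Hz filter. Peaks were found by the written rule, with and without a parabola through the three samples around each peak.

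| True RMSSD (ms) | Written rule (ms) | With parabola (ms) |
|---|---|---|
| 5 | 16.1 | 5.1 |
| 10 | 17.2 | 10.2 |
| 20 | 24.6 | 20.4 |
| 40 | 42.7 | 40.8 |

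A second set of synthetic waves gave 16.7 and 9.3 ms for a true 10.1 ms, and 19.8 and 13.8 ms for a true 15.1 ms. The parabola removes most of the error, with a small remainder in either direction depending on the waveform. The cause is thus the unrefined peak position and not the sampling rate.

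**Step 6: effect on correlation with a target.** Two simulations assumed log-normal RMSSD across people.
- 885 people, true correlation 0.3 with log RMSSD, median RMSSD 10-25 ms: the correlation fell by about 3-6%.
- 3,000 recordings of 375 beats, log-SD 0.4 or 0.6: rounded and unrounded RMSSD correlated at 0.993-0.998 for medians of 20-30 ms and at 0.975-0.984 for a median of 12 ms. Correlation with the target moved from 0.188 to 0.183 at a median of 20 ms and from 0.191 to 0.180 at 12 ms. The loss was about 1-5% for medians of 20-30 ms and 6-7% at worst.

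**The case against.** The strongest objection is that the missing refinement is inferred from silence. The article condenses a pipeline reported elsewhere and describes the rule as a first detection of potential peaks, which could mean candidates that are later refined. Interpolation is a detail that an article may leave to its source. This stands as a limit on certainty: the document does not prove that the final beat times lie on the grid. It does not remove the point. The article gives the filter, the outlier rule and the detection rule step by step, sends the resulting positions to feature extraction, and names no sub-sample step.

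A reader might infer that 50 Hz is too slow, or that the statement in Photoplethysmography Data Collection is wrong. Neither is supported. The sentence claims adequacy for heart rate, where the error is negligible, and the remedy works at 50 Hz.

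A reader might also infer that useful features are lost on a large scale, or that the reported accuracy is biased. The documents do not support that either. The observed value rises steadily with the true value, so the ordering of participants largely survives and the loss of correlation is small. HR-variability features are optional inputs, not endpoints. They pass two selection stages, and performance is judged on participants kept apart from the training folds. Noisier inputs would tend to lower measured accuracy; they would not falsify it.

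Finally, the large percentages need a low true RMSSD, which the documents do not give. That is correct, and it is why a range is shown.

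**Conclusion.** The point holds as a cheap improvement to the stated method. Applied as written, the rule puts beat times on a 20 ms grid and adds about 14.1 ms in quadrature to RMSSD. Inflation is 73% at a true 10 ms, 22% at 20 ms, 11% at 30 ms and 6% at 40 ms. The expected loss of correlation with a target is roughly 1-7%, enough to displace a borderline feature in the correlation screen and little more. Mean heart rate and the validity of the reported accuracy measures are not in question.

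This rests on three assumptions: that the cited pipeline adds no refinement, which cannot be checked here; that the panel contains measures based on successive differences, which the article does not list; and that the assumed RMSSD levels and distributions are realistic. Complexity features use the same positions, but the effect on them was not quantified.

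**What to change.** In Photoplethysmography Data Feature Extraction, add a step before HR-variability and complexity features are computed. It should refine each peak and trough time below the sample step, either by fitting a parabola through the three samples around the extremum and taking its vertex, or by upsampling the filtered signal (for example by spline or band-limited interpolation to at least 500 Hz). The filtered band ends near 5 Hz, well below the 25 Hz Nyquist limit, so the timing can be recovered from the stored signals. Then re-run feature extraction on all recordings.

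If the pipeline already does this, one sentence in that section settles the point. If it does not and a re-run is unwanted, a sensitivity analysis without the short-term HR-variability features would show whether they matter.

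The cost is a few lines of code and one re-run, with no new data. The drawback is that these features will differ slightly from those of the earlier Singapore pipeline unless that dataset is re-run the same way.
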